**F. Data Analysis**

Outcome Measures: Two outcome measures will be used at baseline and endpoint of this study:

Allergic symptoms questionnaire:

Participants will be asked to assess their allergic symptoms by using a questionnaire describing different symptoms (itching, prickling, or burning feelings in the nose; constipated or running nose; impaired sense of smell or taste; sneezing fits; feeling like having a cold; itching or irritated skin; eczema on the skin; itching, burning or red eyes; billowed eyelids; itching, prickling or scratching feelings in the throat; sore throat; burning feeling or mucus in the mouth or throat; billowed mucosa; breathlessness; cough; headaches; feelings of exhaustion; lack of concentration; tiredness; disorders of the gastrointestinal tract). The patients will indicate their response on a seven-point scale ranging from ‘never’ (1) to ‘always’ (7). For further analysis we will calculate a composite score including all symptoms (see Schaefer et al., 2016). This is the primary outcome parameter.

Quality of Life (SF36): The SF-36 is a German version of the health survey developed by Ware and Sherbourne (1992) in order to examine subjective well-being and quality of life. This instrument assesses the quality of life with respect to the perception of the health both for patients and healthy people. It includes one multi-item scale that assesses different health concepts such as limitations in physical activities because of health problems, limitations in social activities because of physical or emotional problems, limitations in usual role activities because of physical health problems, bodily pain, general mental health (psychological distress and well-being), limitations in usual role activities because of emotional problems, vitality (energy and fatigue), and general health perceptions.

Planned Statistical Analyses

We will conduct analyses of variance (ANOVA) with three factors (time, placebos, information on the power of placebos) for allergic symptoms as well as for quality of life scores. In addition, we will test if baseline scores are different. All tests will be two-tailed with alpha set at .05.

Statistical Power

Based on effect sizes of our previous study (Schaefer et al., 2016), we will need 104 participants for an alpha set at .05. However, given that this is a pilot study and data collection is limited due to weather (pollen) conditions, we aim to include 60 patients in this study.

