**E. Description of Research Protocol**

Overview: This study aims to test whether non-deceptive administration of placebo in patients with allergic rhinitis will be superior to a control group, and if this effect is independent of detailed information on positive effects of placebos.

Design: 60 patients with allergic rhinitis will be randomized to a two-week course of either non-deceptive placebo pill with detailed information on positive effects of placebos, of non-deceptive placebo pill without detailed information on positive effects of placebos, of no treatment plus usual care with detailed information on positive effects of placebos, and of no treatment plus usual care without detailed information on positive effects of placebos. All groups will receive the same amount of time with the practioner. Participants will be assessed at baseline and at the end of the two weeks.

Design and intervention:

Description of the open-label placebo treatment arms:

After signing the informed consent the patients will be assessed with respect to their allergic symptoms and quality of life. They will be told to note their allergic complaints at the end of each day in an allergic diary. Then they will receive 28 placebos in a white box, labeled with the logo of the university and the following information “Placebo pills (28), take one in the morning and one before night, for 14 days”

Description of the no treatment usual care control arms:

This control group will be treated as the open-placebo group, but do not receive any placebos. The purpose of this control group is to match for time with practioner and to assess general improvements of allergic symptoms due to changes in weather (pollen) conditions.

Description of the detailed information on placebo arms:

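### The planned time-by-treatment ANOVA tests raw change scores; adjusting the endpoint for baseline would generally be more precise, at the cost of one error degree of freedom

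*Protocol*

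**What the plan says.** Section E randomises patients to four groups formed by placebo (yes/no) and detailed information (yes/no). On timing it says: "Participants will be assessed at baseline and at the end of the two weeks". Section F confirms the two visits for both outcomes: "Two outcome measures will be used at baseline and endpoint of this study". The composite allergic-symptom score is the primary outcome.

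Section F then fixes the model: "We will conduct analyses of variance (ANOVA) with three factors (time, placebos, information on the power of placebos) for allergic symptoms", and applies it to quality of life as well. It adds: "In addition, we will test if baseline scores are different". On error rates: "All tests will be two-tailed with alpha set at .05". It names no baseline covariate, does not say which ANOVA term decides the trial, and attaches no consequence to the baseline test.

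On size, the same section says "we will need 104 participants for an alpha set at .05" and then "we aim to include 60 patients in this study". The basis is given only as "Based on effect sizes of our previous study". Effect size, target power, allocation ratio and baseline-endpoint correlation are not stated.

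**The concern.** With one baseline and one endpoint value per patient, an interaction of any between-patient factor with time is a comparison of endpoint minus baseline. That fixes the slope of endpoint on baseline at 1. A model with baseline as a covariate estimates the slope from the data, and in a randomised comparison it generally has the smaller error variance. The protocol accepts 60 patients against its own figure of 104, so precision is scarce.

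Section D also predicts that information will not interact with the placebo effect. Support for that prediction depends on how tightly the interaction is estimated.

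The baseline significance test does not help. Under randomisation its null hypothesis is true by design, so it measures only chance, and a chance imbalance is not corrected by testing for it.

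**Working it through.** **Inputs from the protocol.** Two assessments (E, F); three-factor ANOVA without covariate (F); two-sided alpha 0.05 (F); 104 needed, 60 planned (F).

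**Assumptions, because the protocol gives no figure.** 15 patients per cell, so 30 v 30 for placebo; baseline-endpoint correlation rho from 0.3 to 0.9; 104 set for 80% power for a two-level factor, with the effect standardised by the SD of change. Other targets are shown below.

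**The plan's own figure.** The 104 cannot be verified without effect size and power. It can be back-solved: 2(1.96 + 0.842)^2 / 0.55^2 = 51.9, so 52 per group and 104 in total. With the noncentral F (1 and 100 df), 104 corresponds to d = 0.555 at 80% power, 0.642 at 90% or 0.714 at 95%.

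**Identity.** In one simulated data set of 60, the time x placebo F from the mixed ANOVA and the placebo F from an analysis of change scores were both 4.774 on 1 and 56 df. By the same identity, the three-way term is the placebo x information test on change scores. This covers only the terms that include time. The placebo main effect averages baseline with endpoint and is a much weaker test: simulated power is about 35%, 23%, 15% and 8% at rho 0.3, 0.5, 0.7 and 0.9.

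**Variance ratio.** With equal variances at both visits, scaled to 1:

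- change score: 2(1 - rho)
- baseline-adjusted: 1 - rho^2
- ratio: (1 - rho^2) / [2(1 - rho)] = (1 + rho)/2

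**Power at N = 60.** Planned test: noncentrality 0.555 x sqrt(60/4) = 2.15 on 56 df, giving 56%. Adjusted test: d divided by sqrt[((1+rho)/2)(1 + 1/54)] on 55 df, where 1/54 allows for chance baseline imbalance.

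| rho | variance ratio | planned | adjusted | simulated, planned / adjusted | adjusted N matching 104 |
|---|---|---|---|---|---|
| 0.3 | 0.65 | 56% | 74% | 55% / 74% | 68 |
| 0.5 | 0.75 | 56% | 68% | 56% / 68% | 78 |
| 0.7 | 0.85 | 56% | 62% | 56% / 62% | 88 |
| 0.9 | 0.95 | 56% | 57% | 55% / 57% | 99 |

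Simulations used 6,000 runs per rho. At rho 0.99 the calculated adjusted power is 55.5%, so the lost degree of freedom outweighs the gain, by less than one point.

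**Other readings of 104.** For a 90% target, the planned test has 69% at N = 60 and the adjusted test 85%, 80%, 75% and 70% over the same rho values. For a 95% target, 78% becomes 92%, 87%, 83% and 79%. If d is standardised by the endpoint SD instead (80% target), planned v adjusted is 43% v 59%, 56% v 68%, 78% v 83%, and above 99% for both.

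**Making up the shortfall.** Adjustment lets 60 patients do the work of 104 only if 104(1+rho)/2 is at most 60, that is, rho at most 2 x 60/104 - 1 = 0.15.

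**Unequal variances.** With k = endpoint SD / baseline SD, the ratio is (1 - rho^2)k^2 / (1 + k^2 - 2 rho k). The denominator exceeds the numerator by (1 - rho k)^2, so the ratio never exceeds 1, but its size moves. At rho 0.7 it is 0.63 for k = 0.8, 0.85 for k = 1, 0.97 for k = 1.2 and 0.99 for k = 1.3.

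**Interaction.** With 15 per cell and rho 0.5, the 95% CI half-width in endpoint SDs is 2.00 x sqrt(4/15) = 1.03 for change scores and 2.00 x sqrt(0.75 x 4/15) = 0.90 with adjustment.

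**Chance imbalance.** The SD of the baseline difference is sqrt(2/30) = 0.26 baseline SDs for 30 v 30 and sqrt(2/15) = 0.37 for two cells. With equal variances, the change score carries (1 - rho) of the observed difference, with reversed sign, into the estimate.

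**The case against.** The strongest reply is that nothing in section F is an error. A mixed ANOVA is a standard, valid analysis of a randomised 2 x 2 design with two visits, and nothing stops an SAP, which is not at hand, from adding a covariate. Validity stands. But the protocol itself fixes the model, so this is not a detail merely left open.

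A reader might infer that the planned analysis is biased because chance baseline differences enter the estimate. The documents do not support that. Patients are randomised, and over randomisation the change-score estimate is unbiased; the carry-over exists only conditionally on the imbalance that happens to occur.

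A reader might also infer that adjustment always raises power and costs nothing. It costs one error degree of freedom, and the gain depends on rho, which is not given. The same 20-odd symptoms are rated again after two weeks in patients asked not to change their usual medication (section I), so a correlation above 0.7 cannot be excluded. Section E expects pollen conditions to shift symptoms, so equal SDs are not assured either. These points limit the size of the gain; they do not reverse its direction over the practical range.

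The 56% is not the protocol's figure, since it rests on an assumed 80% target. That stands, and the alternatives are shown above.

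Finally, the baseline test alters no estimate and no decision depends on it, so its removal is a minor matter.

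**Conclusion.** The point holds as a loss of efficiency. The terms that carry the treatment effect are change-score tests, and adjusting for a baseline already collected would generally be more precise. Under equal variances, 30 v 30 patients and 104 meaning 80% power on the change-score scale, the gain at N = 60 is about 18, 12, 6 and 1 percentage points at rho 0.3, 0.5, 0.7 and 0.9. Above rho of about 0.95 there is none. If the SDs at the two visits differ, the gain may be larger or close to nil.

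It would be too much to conclude that adjustment repairs the shortfall. That would need rho of about 0.15 or less, which is unlikely for one questionnaire repeated after two weeks, though the protocol gives no value. The change is worth making because it is cheap and the trial is short of patients, not because the planned analysis is invalid.

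**What to change.** Make the primary model a linear model of the endpoint composite on baseline composite, placebo, information and placebo x information.

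Specify sum-to-zero coding, or a marginal placebo contrast averaged over the two information levels, so that the placebo effect uses all 60 patients. This matters: under 0/1 coding the placebo coefficient in a model with the interaction is a simple effect in one information stratum, about 15 v 15, with roughly 41% power at rho 0.5 on the same assumptions. That is worse than the planned test.

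Report the adjusted placebo effect and the adjusted interaction with 95% CIs, and use the same model for quality of life. Keep the three-factor ANOVA as a sensitivity analysis. Replace the baseline significance test with a description of baseline by arm.

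The cost is a change of analysis wording and one error degree of freedom (56 to 55). No new data, visits or patients are needed.

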**B. Background for the Study**

Recent research has demonstrated that placebo treatment can have significant impacts for a wide variety of symptoms (Finiss et al., 2010). Unfortunately, in the traditional understanding response to placebos requires deception. This may cause problems with respect to patient-healthcare provider relationship and ethical difficulties. In contrast to this classic view recent research has demonstrated that placebos may work even without concealment. For example, Kaptchuk et al. (2010) conducted a randomized controlled trail including patients with irritable bowel syndrome. Half of the patiens received placebos without deception, the other half served as a control group. The authors found significantly higher mean global improvement scores, reduced symptom severity, and better quality of life scores for the open-placebo group. Similar results have been reported, for example, for patients with major depression (Kelley et al., 2012) and ADHD (Sandler et al., 2008).

Our previous study has demonstrated that open-label placebos also improve

symptoms in patients with allergic rhinitis (Schaefer et al., 2016). However, this pilot study was based on only few patients. Thus, we here want to replicate the results in a larger sample.

Furthermore, the mechanism of open-label placebo effects remains unclear. Are open-label placebo effects based on bottom-up mechanisms, such as classical conditioning? Or are they linked to raised expectancies about the positive effects of placebos in general, hence representing top-down effects? The latter may be related to the detailed information on the power of placebo effects. This information is included in nearly all open-label placebo studies. In order to disentangle top-down and bottom-up effects, we aim to manipulate this information: Half of the participants will be informed about the power of placebos, the other half not.

We expect to replicate the previous findings that open-label placebos improve allergic symptoms more than in a control group with comparable patient-healthcare provider relationships. Furthermore, we assume that the open-label placebo effect is independent of the information how powerful placebos are, thereby suggesting a bottom-up effect.

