**D. Hypothesis**

In allergic rhinitis patients, a two weeks course of open-label non-deceptive placebo treatment will be superior to no treatment plus usual care control. In addition, information on the positive effects of placebos will not interact with this open-label placebo effect.

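### The planned ANOVA terms do not show that placebo pills work in uninformed patients, so a non-significant interaction alone cannot support the bottom-up reading

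*Protocol*

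**What the plan says.** Section E of the protocol randomises 60 patients to a two-by-two design, pills or no pills crossed with information or no information. Two arms receive no information: one is given a "non-deceptive placebo pill without detailed information on positive effects of placebos", the other "no treatment plus usual care without detailed information on positive effects of placebos".

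Section D puts forward two hypotheses. Placebo is superior to the control, and "information on the positive effects of placebos will not interact with this open-label placebo effect". Section B attaches a mechanism to the second: "we assume that the open-label placebo effect is independent of the information how powerful placebos are, thereby suggesting a bottom-up effect".

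For the analysis, Section F states: "We will conduct analyses of variance (ANOVA) with three factors (time, placebos, information on the power of placebos". This applies to symptoms and to quality of life, and a comparison of baseline scores is added. The error rate is fixed by "All tests will be two-tailed with alpha set at .05". On size, Section F says "we will need 104 participants for an alpha set at .05", but then plans 60, citing the pilot nature of the study and the pollen season. It gives no effect size, standard deviation or power.

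**The concern.** The mechanism argument has two parts: a placebo effect exists, and it does not depend on the information. The time-by-placebo term addresses the first part for all patients together. The time-by-placebo-by-information term addresses the second, but only by asking whether two effects differ. If the first is significant and the second is not, the reader is invited to conclude that pills work without the script. That pattern is also compatible with no effect at all in uninformed patients. The pooled effect can be carried by the informed arms while the interaction goes undetected.

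The direct evidence is the pill minus no-pill difference among uninformed patients. The design provides for it, but Section F does not name it. At stake is whether the trial can report a bottom-up effect when its own uninformed arms show little or nothing.

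**Working it through.** **Inputs.** From the protocol: total 60, calculated requirement 104, two-sided alpha .05, four arms. Assumed: equal allocation (15 per arm), normally distributed change scores with SD 1, no dropout, and a common error term with 60 − 4 = 56 degrees of freedom.

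**The figure of 104.** It cannot be reproduced, because no effect size or power is given. Solving backwards for two groups of 52 gives d = (1.960 + z_power) / √(52/2):

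- 80% power: d = 0.549
- 90% power: d = 0.636
- 95% power: d = 0.707

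A standardised effect of about 0.55 to 0.71 is therefore a plausible reading of the planning assumption, but only an inference.

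**The contrasts.** Let P_I, P_U, C_I and C_U be the mean changes for pills informed, pills uninformed, control informed and control uninformed.

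- Pooled effect: M = [(P_I − C_I) + (P_U − C_U)] / 2, SE = √(1/15) = 0.258
- Interaction: X = (P_I − C_I) − (P_U − C_U), SE = √(4/15) = 0.516
- Uninformed effect: U = P_U − C_U = M − X/2, SE = √(2/15) = 0.365

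The last line shows that U needs no new model, since it is a combination of the two planned terms.

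**Effect in informed patients only.** If P_I − C_I = D and U = 0, then M = D/2 and X = D. The noncentralities are (D/2)² / (1/15) = 3.75 D² for the pooled test and D² / (4/15) = 3.75 D² for the interaction. The two tests have the same power, so the interaction is no more likely to flag the problem than the pooled test is to create it. Results from the noncentral F distribution (1 and 56 df) and 200,000 simulated trials per row:

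| D (SD of change) | Power of each test | Pooled significant, interaction not | Interaction non-significant, given pooled significant | As third column, and uninformed contrast also significant |
|---|---|---|---|---|
| 0.55 | 18% | 15% | 81% | 2% |
| 0.8 | 33% | 22% | 65% | 2% |
| 1.0 | 48% | 25% | 52% | 2% |
| 1.1 | 55% | 24% | 43% | 2% |
| 1.5 | 82% | 15% | 18% | 2% |

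The third column is close to p(1 − p), where p is the common power. This peaks at 0.5 × 0.5 = 0.25, hence the ceiling of about 25%.

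**Precision of the uninformed contrast.** With 15 per arm and the 56-df error term, its power is about 32% at d = 0.55, 40% at 0.64 and 48% at 0.71. The 95% CI half-width is 2.003 × 0.365 = 0.73 SD, and for the interaction 2.003 × 0.516 = 1.03 SD. For 80% power at d = 0.55 the contrast would need 52 per arm, or 4 × 52 = 208 patients in total.

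**The case against.** The strongest reply is that Section D frames the second hypothesis as absence of interaction, and the three-factor ANOVA contains exactly that interaction. Section B is worded as an expectation, not a reporting rule. Follow-up contrasts are commonly left to a statistical analysis plan, which is not available here. This stands in part. A reader might infer that the uninformed arms will never be compared, or that the comparison would be dropped once the interaction is non-significant. The protocol says neither. What remains is that it names its tests and also names the mechanism it hopes to read from them, and those tests do not carry that reading.

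A second reply concerns size. One could take d = 0.55 as the pooled effect, place all of it in the informed arms (D of about 1.1), and quote 24%. Sections B and E say that nearly all previous open-label studies gave this information and that the four statements match those used before. The earlier effect is thus more plausibly an informed-patient effect, which gives about 15%. The 24% is close to the mathematical maximum and should not be read as an expected rate.

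A third reply is that making the mechanism claim depend on a significant uninformed contrast would be harsh. If the effect really is equal in both strata (0.555 each), the pattern of pooled significant and interaction non-significant occurs in about 53% of trials, and only about 27% would also pass the contrast. Passing would not show independence either, because an uninformed effect above zero is compatible with a much larger informed one. This is correct. It argues for reporting both intervals and against a single significance gate as proof of independence.

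**Conclusion.** The concern holds in a limited form. The pooled placebo effect and the interaction, taken as two significance tests, do not establish that placebos work in uninformed patients, and Section B's bottom-up reading needs that evidence. If the effect is confined to informed patients, the misleading pattern arises in about 15% of trials at 0.55 SD, 22% at 0.8 SD, and never much above 25%. These figures assume equal arms of 15, normal change scores and complete data. The effect sizes are not in the protocol.

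A stronger reading would be that the superiority test is flawed or that the trial will report a false mechanism. The document supports neither. The pooled time-by-placebo test remains a proper test of the first hypothesis, and the size of any uninformed effect is unknown. This is an inexpensive improvement to what the trial may conclude.

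**What to change.** In Section F, keep the pooled time-by-placebo test for superiority and add three statements for the primary symptom composite:

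1. The difference in change between the uninformed pill arm and the uninformed no-pill arm will be estimated with its 95% CI, using the four-arm error term.
2. It will be reported alongside the time-by-placebo-by-information estimate with its 95% CI.
3. A non-significant interaction alone will not be taken to support independence from the information or a bottom-up effect. If the uninformed CI includes zero, the mechanism question will be reported as inconclusive, not as evidence of no effect.

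The cost is one contrast from the model already planned and a few sentences of text, with no new patients or data. The price is a harder mechanism claim. With about 30 patients and about 32% power at d = 0.55, the uninformed CI will often include zero and the question will often stay open.

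### The superiority hypothesis is tied to no single ANOVA term: two terms could be reported as the placebo effect (about 10% two-sided error on the primary outcome), and neither is the most precise test available

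*Protocol*

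**What the plan says.** Protocol section D states two hypotheses in words. The first is that "a two weeks course of open-label non-deceptive placebo treatment will be superior to no treatment plus usual care control". The second is that "information on the positive effects of placebos will not interact with this open-label placebo effect".

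Section F, under the outcome measures, says of the symptom composite: "This is the primary outcome parameter". The planned analysis reads "We will conduct analyses of variance (ANOVA) with three factors (time, placebos, information on the power of placebos"), to be run "for allergic symptoms as well as for quality of life scores". Baseline comparisons are added, and one sentence covers all of it: "All tests will be two-tailed with alpha set at .05".

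The protocol links neither hypothesis to a term of the ANOVA and states no order or adjustment among the tests. On the SF-36 it says "It includes one multi-item scale that assesses different health concepts", lists several concepts, and does not say how many scores will be analysed.

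**The concern.** A primary outcome is fixed, but a primary effect is not. A three-factor ANOVA produces seven F tests, and the protocol gives all seven the same standing.

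The term that carries the factor's name, the placebo main effect, averages the baseline and endpoint scores. Treatment cannot have changed the baseline score, so this term halves the effect. Time x placebo compares the change between groups and is the term that fits the hypothesis. An analyst holding both results could report either as the placebo effect, and nothing in the protocol prevents this.

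Two things are at stake. One is an error rate above the stated .05 for the main claim. The other is precision, in a trial that plans 60 patients after stating that 104 are needed.

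A second problem follows from the same rule. The information hypothesis predicts no interaction, and the only inferential tool named is a test at .05. A non-significant F test cannot show that an interaction is absent.

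**Working it through.** **Inputs from the protocol.** Two-sided alpha of .05 for every test; three two-level factors; 60 patients in four groups; baseline and endpoint assessments. **Assumed, because not stated.** Equal allocation (15 per group, 30 v 30 for placebo against control); equal SD at both times; baseline-endpoint correlation rho of 0.3, 0.5 or 0.7.

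**Step 1. The plan's own figures.** The protocol gives no familywise error rate to reproduce. Its 104 comes without effect size, SD or power, so it cannot be verified. In a two-arm normal approximation it back-solves to d = 0.55 at 80% power, 0.64 at 90% or 0.71 at 95%.

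**Step 2. Count the terms.** 2^3 - 1 = 7 per score.

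| Term | Bearing on the hypotheses |
|---|---|
| Time | None; section E uses the control arms to capture pollen-related change |
| Information | None on superiority |
| Time x information | None on superiority |
| Placebo | Could be reported as superiority; diluted by baseline |
| Time x placebo | Fits the superiority hypothesis |
| Placebo x information | Would count against the second hypothesis; diluted by baseline |
| Time x placebo x information | Would count against the second hypothesis |

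**Step 3. Error rates**, from 1 - 0.95^k. The second column is a simulation of the mixed ANOVA under the complete null (15 per group, 200,000 trials, correlation 0.3 and 0.6).

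| Terms that may count | Formula | Simulated |
|---|---|---|
| 1 (time x placebo) | 0.050 | 0.050 |
| 2 (placebo, time x placebo) | 1 - 0.95^2 = 0.0975 | 0.097-0.098 |
| 4 (all containing placebo) | 1 - 0.95^4 = 0.185 | 0.183-0.186 |
| 7 (any) | 1 - 0.95^7 = 0.302 | 0.295-0.299 |

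**Step 4. What each candidate term measures.** Let the endpoint effect be delta, with none at baseline, and the SD sigma at both times.

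- Placebo main effect: delta/2 over sigma x sqrt((1+rho)/2), so relative size 0.5/sqrt((1+rho)/2).
- Time x placebo: delta over sigma x sqrt(2(1-rho)), so 1/sqrt(2(1-rho)).
- Baseline-adjusted placebo term: delta over sigma x sqrt(1-rho^2), so 1/sqrt(1-rho^2).

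| rho | Main effect | Time x placebo | Baseline-adjusted |
|---|---|---|---|
| 0.3 | 0.62 | 0.85 | 1.05 |
| 0.5 | 0.58 | 1.00 | 1.15 |
| 0.7 | 0.54 | 1.29 | 1.40 |

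The adjusted term exceeds time x placebo by the factor sqrt(2/(1+rho)) and the main effect by sqrt(2/(1-rho)). Both factors are above 1 at any positive correlation below 1, so the ordering does not depend on the value assumed.

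**Step 5. What this means for 60 patients.** The variance ratio of the adjusted term to time x placebo is (1+rho)/2. At rho = 0.5 that is 0.75, so 60 patients analysed with adjustment are worth 60/0.75 = 80 on time x placebo (60/0.65 = 92 at rho = 0.3; 60/0.85 = 71 at 0.7).

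As an illustration, take d = 0.549 as the endpoint effect (the 80% back-solve), 30 v 30 and rho = 0.5. The expected z for a relative size of 1.00 is 0.549 x sqrt(15) = 2.13. Power, Phi(z - 1.96), is then about 57% for time x placebo, 23% for the main effect (z = 0.577 x 2.13 = 1.23) and 69% for the adjusted term (z = 1.155 x 2.13 = 2.46).

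**Step 6. The interaction.** With 15 per group, the difference of differences has standard error sqrt(4/15) = 0.52 residual SD, so the 95% interval extends 1.96 x 0.52 = 1.01 residual SD either side. A non-significant result would be compatible with a sizeable interaction.

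**The case against.** The best defence is that the protocol already points to the answer. The primary outcome is named, the hypotheses are stated, and with time in the model time x placebo is the natural reading. Naming the confirmatory term is also commonly left to a statistical analysis plan, which may exist here. Most of this stands: a missing label alone would be close to missing detail. But the protocol itself fixes the model and the rule for all tests. That model is not the most precise one, and its rule leaves a hypothesis of no interaction to a significance test. Those two points go beyond a label.

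A reader might infer that the seven tests mean a 30% risk of a false claim. The documents do not support that. The 30% is the chance that some term is significant under a complete null, including no change over time. Time, information and time x information cannot support superiority, and the two terms crossing placebo with information would speak against the trial's own prediction. Two terms remain. Counting only results that favour placebo, the error is 1 - 0.975^2 = 4.9%, against 2.5% for one term.

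A reader might also see a contradiction between "It includes one multi-item scale that assesses different health concepts" and "as well as for quality of life scores", and go on to 34% (1 - 0.95^8, eight time x placebo tests) or 56% (1 - 0.95^16, adding the three-way terms). The word scores may simply mean patients' values on one scale. Those figures need eight separately and independently tested subscales, which the protocol nowhere states. The SF-36 is not the primary outcome, so this is a point to clarify.

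Finally, the correlations are assumed, and the loss of power arises only if the main effect is the term actually used. Both are fair. The ordering of the three terms nevertheless holds at any positive correlation.

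**Conclusion.** The point holds in limited form. The superiority hypothesis is not bound to one term, and two terms could be reported as the placebo effect, giving about 10% two-sided error on the primary outcome instead of 5%. The wider count of four terms gives about 19%. These figures assume that any of the counted terms would be accepted as support, which the protocol leaves open but does not plan.

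The larger practical gain is in precision: a baseline-adjusted placebo term is better than either ANOVA term at any positive baseline-endpoint correlation, by an amount that depends on a correlation the protocol does not give. The planned test also cannot establish that information makes no difference. The change is worth making because it costs almost nothing; the point does not show that the trial's main comparison is invalid.

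**What to change.** Amend the analysis paragraph of section F along these lines:

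- The single confirmatory test, at two-sided .05, is the placebo term in a linear model of the endpoint symptom composite, with baseline composite, placebo, information and their interaction. Code the factors so that the placebo term is the average effect over the two information conditions.
- Report the placebo x information interaction from the same model as an estimate with a 95% confidence interval. State that non-significance will not be read as proof of no interaction.
- All other terms, the three-factor ANOVA if it is kept, and the SF-36 results are secondary or descriptive.
- State which SF-36 score or scores are analysed. A Holm adjustment across them is optional.

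The cost is a few sentences and fewer results that can be called significant. No extra data are needed, since the baseline score is already collected.
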